**◎ Action taken**

0 = No action taken

1 = Temporary discontinuation of study drug administration

2 = Discontinuation of study drug administration

3 = Medical intervention

4 = Non-medical intervention

5 = Hospitalization

**◎ Report of AE**

At Visit 2, Study personnel will directly observe study subjects for 30 minutes after taking study drug for immediate reactions. The subjects also observed during TMS procedure and until 30 min after examination. Study personnel will ask the degree of pain (Visual analogue scale) immediately after TMS. The occurrence and severity of any AE by study drug or device during this visit will be recorded on the appropriate CRF. The subjects will be asked to note and characterize in their own words about any local or systemic AEs they experience, during 7-day period between visit 2 and 3.

At visit 3, study subjects will be queried regarding the occurrence of any SAE or other unexpected AE that may have occurred since the last visit. These events will be recorded on the CRFs.

The reporting period for AEs is the period starting from the time of administration of study drug to the day of study completion (visit 3).

Events that involve a death or are unexpected, serious and related or possibly related to the investigational drug will be submitted to the Pfizer Inc. within 24 hours of discovery. In case blinding code inevitably needs to be broken for treatment of subject, investigator must report it to the Pfizer Inc. within 24 hours of discovery.

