| Number of study subject | A total of 40 subjects  Study 1 (EEG study) - Celecoxib: 10 subjects/ placebo: 10 subjects  Study 2 (TMS study) - Celecoxib: 10 subjects/ placebo: 10 subjects |
| Vulnerable subjects | Employees |
| Study methods | Celecoxib  - Dose: 400mg/day  - Route of administration: oral  - Duration of administration: 7 days  Study 1  - After randomization, EEG will be performed at baseline just before celecoxib (400 mg) or placebo delivery at 9 AM. EEG will be repeated 4 hours after the administration. The subjects will take celecoxib or placebo 200 mg twice a day for 7 subsequent days, and a third EEG will be conducted 4 hours after the final dose.  Study 2  - After randomization, TMS will be performed at baseline just before celecoxib or placebo (200 mg) delivery. The subjects will take 200 mg of celecoxib or placebo twice a day for 7 days. The second TMS recording will be performed 4 hours after the final dose. |
| Efficacy evaluation | Study 1  Primary end point  - Change of power spectra by single high dose of celecoxib.  Secondary end point  - Change of power spectra by 7-day treatment.  - Change of electroencephalographic properties by celecoxib in specific locations or frequency band by single dose or 7-day treatment.  Study 2  Primary end point  - Change of resting motor potential, amplitude of MEP, cortical silent period, intracortical inhibition and intracortical facilitation by 7-day treatment of celecoxib |
| Adverse effect evaluation | Adverse effect or serious adverse effect  All the adverse events including status changes after enrollment will be recorded, regardless of causal relationship to study drug or examination.  The subjects will be observed directly for 30 minutes after taking study drug for immediate reactions. The subjects also will be observed during TMS procedure and until 30 min after examination. The subjects will be asked if they had any pain (by Visual analogue scale) immediately after TMS. The occurrence and severity of any adverse events by study drug or device during this visit will be recorded on the appropriate CRF |
| Expected result | The knowledge from this research will deepen our understanding about inflammation and neuronal activity and will be a basis of clinical study for utilizing celecoxib as an anticonvulsant in the future. |

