**Study 2**

◎ Epidemiologic data

- Age, date of birth, age

- Medication history

- Medical history

- Physical examination

◎ Laboratory data

- Blood lab: AST/ALT, serum creatinine, potassium

- EKG

- Motor evoked potential (MEP)

- A figure-of-eight shaped magnetic stimulator will be located over the contralateral motor cortex to produce optimal motor potentials in the first dorsal interosseous muscle.

1) The resting motor threshold (RMT): the lowest intensity required to evoke MEPs in the FDI with a peak-to-peak amplitude of at least 50 μV in 4 of 8 trials

2) Peak-to-peak amplitude: With the FDI muscle in the relaxed state, stimuli will be delivered to evoke MEPs at stimulus intensities of 120%, 140%, and 150% (if possible) of RMT. [16]. Eight stimuli will be delivered randomly at each stimulus intensity every 5 seconds, and the average of the peak-to-peak amplitudes will be measured

3) Cortical silent period: The time between the end of the stimulus-induced MEP and the reoccurrence of voluntary EMG activity,

| Primary end point  - Change of resting motor potential, amplitude of MEP, cortical silent period, intracortical inhibition and intracortical facilitation by 7-day treatment of celecoxib |
| --- |

| **Study 1** | Screening  (Visit 1) | Visit 2(1^st^ day) | 2^nd^ day ~ 6^th^ day | Visit 3 (7^th^ day) |
| --- | --- | --- | --- | --- |
| Informed consent | V |  |  |  |
| Age, date of birth, age | V |  |  |  |
| Medication history | V |  |  |  |
| Medical history | V |  |  | V |
| Physical examination | V |  |  |  |
| Blood lab | V |  |  |  |
| EKG | V |  |  |  |
| Study drug administration |  | V | V | V |
| Adverse event |  | V |  | V |
| EEG |  | V (2 times) |  | V(once) |

| **Study 2** | Screening  (Visit 1) | Visit 2(1^st^ day) | 2^nd^ day ~ 6^th^ day | Visit 3 (7^th^ day) |
| --- | --- | --- | --- | --- |
| Informed consent | V |  |  |  |
| Age, date of birth, age | V |  |  |  |
| Medication history | V |  |  |  |
| Medical history | V |  |  | V |
| Physical examination | V |  |  |  |
| Blood lab | V |  |  |  |
| EKG | V |  |  |  |
| Study drug administration |  | V | V | V |
| Adverse event |  | V |  | V |
| MEP |  | V(once) |  | V(once) |

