**9) Adverse events (AEs)**

**◎ Definition of AEs**

An adverse event is defined as any unfavorable and unintended change in the structure, function, or chemistry of the body, or worsening of a pre-existing condition, temporally associated with the use of a product whether or not considered related to the use of the product or device. In this study, such changes will be monitored, and summarized.

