**◎ Assessment method for severity of AE**

| 1 = Mild | Awareness of signs or symptoms, but easily tolerated; is of minor irritant; causing no loss of time from normal activities |
| --- | --- |
| 2 = Moderate | Discomfort severe enough to cause interference with usual activities |
| 3 = Severe | Incapacitating with inability to work or do usual activity |

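### The Visit 3 adverse-event query covers only serious or unexpected events, although the protocol promises to record all of them

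*Protocol*

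**What the plan says.** Two general statements set a wide scope. The Adverse effect evaluation row of the Study Summary says: "All the adverse events including status changes after enrollment will be recorded, regardless of causal relationship to study drug or examination". Under item 9 of Study methods, the definition of an AE takes in any unfavorable change during use of the product, related or not, and adds: "In this study, such changes will be monitored, and summarized".

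The operating instructions are under Report of AE in the same item:

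- **Visit 2.** Any AE due to the drug or the device during that visit goes on the CRF, with its severity.
- **Between visits.** "The subjects will be asked to note and characterize in their own words about any local or systemic AEs they experience", over the interval between Visits 2 and 3.
- **Visit 3.** "study subjects will be queried regarding the occurrence of any SAE or other unexpected AE that may have occurred since the last visit". The next sentence reads: "These events will be recorded on the CRFs".
- **Period.** AE reporting starts with study drug administration and ends at Visit 3.

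The visit schedules for both studies tick adverse events at Visit 2 and Visit 3 and leave days 2 to 6 blank.

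**The concern.** The promise is to record all AEs. The sentence that tells staff what to ask at Visit 3, and the sentence that tells them what to write down, cover only serious AEs and other unexpected ones. A subject with non-serious nausea on day 4 has a known effect of celecoxib. If *unexpected* carries its regulatory meaning, that event falls outside both sentences.

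At stake is the AE summary that the protocol promises. The known, non-serious effects are the ones the protocol itself says may occur, so a reader would look for them when comparing celecoxib with placebo. An analysis plan cannot restore events that were never recorded.

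**Working it through.** No arithmetic on rates applies, because the protocol gives no AE rates. The check sets the statements side by side and then counts their scope.

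**Step 1. Scope of each statement**

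| Place in the protocol | Events covered | Limit by seriousness or expectedness |
| --- | --- | --- |
| Study Summary, Adverse effect evaluation | All AEs after enrollment, whatever the cause | None |
| Item 9, Definition of AEs | All such changes, to be summarized | None |
| Report of AE, Visit 2 | Any AE from drug or device during that visit | None |
| Report of AE, subject's own notes | Any local or systemic AE between visits | None |
| Report of AE, Visit 3 query and CRF entry | Serious AEs and other unexpected AEs | Yes |

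The Visit 3 instruction is the only row with such a limit.

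**Step 2. What the Visit 3 query leaves out**

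Crossing serious or non-serious with expected or unexpected gives 2 × 2 = 4 combinations.

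- The clause on serious AEs covers 2: serious expected and serious unexpected.
- The clause on other unexpected AEs covers 1: non-serious unexpected.
- Named: 2 + 1 = 3 of 4. Left out: 4 − 3 = 1, the non-serious expected AEs.

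**Step 3. What falls in the omitted combination**

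Item 7, Risk and benefit of subjects, names seven drug effects: nausea, diarrhea, abdominal pain, stomach upset, rash, facial swelling and insomnia. In the regulatory sense these are expected, so each falls in the omitted combination when it is not serious.

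**Step 4. Whether another step captures them**

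- The Visit 2 entry is confined to that visit.
- The subject's notes are wide enough, but no text says they are collected, reviewed or entered on the CRF. The CRF sentence refers most directly to the serious and unexpected events of the sentence before it.
- The schedule ticks for adverse events, and the repeated medical history at Visit 3, do not say what is asked.
- The reporting period closes at Visit 3, so nothing is planned afterwards.

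**Step 5. What *unexpected* means here**

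The protocol does not define it. The regulatory sense is plausible: the 24-hour reporting rule in the same subsection lists the word next to seriousness and relatedness, and section 12 commits to ICH E2A, a guideline on expedited reporting. An everyday sense is also possible, since item 7 calls the chance of side effects very low. Under that reading the omitted combination may be empty.

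**The case against.** The strongest reply is that the protocol, read as a whole, plainly intends to capture everything. The Study Summary is explicit, and the Visit 3 sentence does not say *only*. The severity scale starts at a grade described as "Awareness of signs or symptoms, but easily tolerated", the causality scale includes unrelated events, and the action scale starts at "0 = No action taken". The dropout criteria refer to any adverse drug reaction, expected or not, and the monitoring plan makes the investigator answerable for complete data. Subjects are asked to note any AE, and the CRF sentence could be read to include those notes. The word *other* in the query also treats serious AEs as a kind of unexpected event, which suits the everyday sense better than the regulatory one. Finally, moving notes to a CRF is often left to CRF instructions, AEs are not an endpoint in either study, and exposure is about a week in 40 volunteers, half of them on placebo.

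Much of this stands. It shows that full capture is intended and that many staff may ask broadly anyway. It also limits the weight of the point. It does not remove the conflict: the one sentence that says what to ask at Visit 3 is narrower than the promise, and narrower than the Visit 2 sentence in the same subsection. That makes it a stated rule at odds with the rest of the protocol, and more than a missing detail. Evidence of a wider intent is a reason to bring the sentence into line.

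**Conclusion.** The concern holds. The Visit 3 query and its CRF entry are narrower than the commitment to record and summarize all AEs, and non-serious known effects arising between visits may be missed. The size can be given only as scope: one of four combinations is left out, and the seven named drug effects belong to it when non-serious.

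This rests on two assumptions: that *unexpected* has its regulatory sense, and that staff follow the sentence as written. If either fails, the gap could be nil. No under-count is claimed. Serious and unexpected AEs are still queried, the Visit 2 entry carries no such limit, and the EEG and TMS endpoints are untouched. The wording should be corrected, but the point does not threaten the trial's main conclusions.

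**What to change.** Reword the Visit 3 instruction under Report of AE so that:

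- subjects are asked about every AE since the last visit, serious or not and expected or not;
- staff review the subject's own notes at that visit;
- every AE found is entered on the CRF.

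Keep seriousness and unexpectedness only as criteria for the 24-hour report to the company.

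The cost is one or two sentences and slightly more CRF entry. No visit is added and no endpoint changes.

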**10) Data and Safety Monitoring Plan**

The principle investigator (an authorized investigator in the absence of the principle investigator) is designated as personnel for data security, and warrants the completeness of the data by collecting and reviewing the data on recruiting every 10 subjects and monitoring about constant safety, and establishes the safety of the study subjects.

**11) Method of analysis**

**Study1**

◎ Change of EEG power spectra by single dose or 7-day treatment of celecoxib or placebo

- Variables between subjects (celecoxib vs. placebo) and within subject (1^st^ EEG vs 2^nd^ EEG, 1^st^ EEG vs 3^rd^ EEG) will be analyzed by student-t test and paired-t test. Analysis of EEG data will consider frequency bands (alpha, delta, theta and beta) and locations (frontal, central and parietal) using repeated measures analysis of variance (rmANOVA). A two-sided 5% significance level will be used for all statistical differences.

**Study 2**

◎ Change of rTMS variables by 7-day treatment of celecoxib or placebo

- Regarding TMS parameters, paired-t-test or Wilcoxon’s signed rank test will be used. RmANOVA will be used for comparison of TMS variables between celecoxib and placebo. A two-sided 5% significance level will be used for all statistical differences.

1. **Study schedule**

|  | Befor May | May | Jun | Jul | Aug | Sep | Oct | Nov | Dec |
| --- | --- | --- | --- | --- | --- | --- | --- | --- | --- |
| - IRB approval | V |  |  |  |  |  |  |  |  |
| - FDA approval | V |  |  |  |  |  |  |  |  |
| - Recruitment and screening |  | V | V | V | V | V | V |  |  |
| - Study |  |  | V | V | V | V | V | V |  |
| - Analysis |  |  |  |  |  |  |  | V | V |
| - Result |  |  |  |  |  |  |  |  | V |

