**Study 1 (Figure)**

EEG will be performed at baseline just before celecoxib (400 mg) or placebo delivery at 9 AM, and EEG will be repeated at 1 PM, 4 hours after administration To evaluate the long-term effects of celecoxib, subjects will take celecoxib or placebo 200 mg twice a day for 7 subsequent days, and a third EEG will be conducted at 1 PM on the last day, 4 hours after the final dose

**
[figure not shown]
**

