**Study 2 (Figure)**

TMS will be performed at baseline just before celecoxib or placebo (200 mg) delivery. The subjects will take 200 mg of celecoxib or placebo twice a day for 7 days. The second TMS recording will be performed 4 hours after the final dose

**
[figure not shown]
**

EEG: electroencephalography; TMS: transmagnetic stimulation

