**5) Analysis**

◎ Analysis

- Per protocol (if needed intention to treat will be used)

◎ EEG power spectra analysis

- 1^st^ EEG vs 2^nd^ EEG: to evaluate acute effect of celecoxib administration.

- 1^st^ EEG vs 3^rd^ EEG: to evaluate long-term effect of celecoxib administration

Variables between subjects (celecoxib vs. placebo) and within subject (1^st^ EEG vs 2^nd^ EEG, 1^st^ EEG vs 3^rd^ EEG) will be analyzed

◎ TMS analysis

- Before and after of 7-days of celecoxib administration. Variables between subjects (celecoxib vs. placebo) and within subject (before vs. after) will be analyzed

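### The between-arm tests in both studies omit baseline as a covariate; ANCOVA would be more precise unless baseline and follow-up correlate very highly, at almost no cost

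*Protocol*

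**What the plan says.** Protocol section 11, item 11) Method of analysis, names the tests.

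- **Study 1.** The between-subject and within-subject comparisons "will be analyzed by student-t test and paired-t test". Frequency bands and "locations (frontal, central and parietal) using repeated measures analysis of variance (rmANOVA") are handled in a further model. The item is headed "Change of EEG power spectra by single dose or 7-day treatment of celecoxib or placebo".
- **Study 2.** Within-subject tests are the paired t-test or Wilcoxon signed rank test. For the arms, "RmANOVA will be used for comparison of TMS variables between celecoxib and placebo". The item is headed "Change of rTMS variables by 7-day treatment of celecoxib or placebo".

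Item 5) Analysis adds for TMS: "Variables between subjects (celecoxib vs. placebo) and within subject (before vs. after) will be analyzed". It gives a matching sentence for EEG, pairing the first recording with the second and with the third.

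A baseline exists for every subject. In Study 1, "EEG will be performed at baseline just before celecoxib (400 mg) or placebo delivery at 9 AM". In Study 2, "TMS will be performed at baseline just before celecoxib or placebo (200 mg) delivery".

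The protocol nowhere makes baseline a covariate. It does not say whether the Study 1 t-test is applied to changes or to follow-up values, or which rmANOVA term is the treatment test.

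**The concern.** With 10 subjects per arm, precision is scarce, and a subject's own pre-dose recording is the best available means of reducing between-subject variation. Subtracting baseline, as a change score does, uses that information fully only when r is close to 1. At lower r, subtraction adds the noise of the baseline recording to the outcome. ANCOVA estimates how much of the baseline to remove.

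The wording also leaves room for two analyses that would serve the trial worse: a t-test on follow-up values that ignores baseline, and an rmANOVA group main effect that averages the pre-dose value into the outcome. At stake are power to detect the planned effect and, for the group main effect, the quantity being estimated.

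**Working it through.** **Inputs** (Protocol, item 3) Sample size estimation): mean difference 0.4; SDs 0.4 and 0.2; two-sided 5%; power 0.8; 10 per group.

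**The plan's own figure.** With z-values 1.960 and 0.842, n = (0.4² + 0.2²)(1.960 + 0.842)² / 0.4² = 0.20 × 7.851 / 0.16 = 9.81, rounded up to 10. The stated 10 per group is reproduced. This is a normal approximation; the noncentral t gives power 0.763 at n = 10 and 0.806 at n = 11.

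**Assumptions added here.** A common SD σ = √((0.4² + 0.2²)/2) = √0.10 = 0.316 in both arms, taken first as the SD of one recording. The correlation r is shown at 0.3, 0.5, 0.7 and 0.9, because the protocol gives no value.

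**Variance of the between-arm estimate** is (2σ²/n) × k:

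- follow-up value only: k = 1
- change score, or group-by-time: k = 2(1 − r)
- ANCOVA: k = 1 − r²
- group main effect over before and after: k = (1 + r)/2, but the expected difference is 0.4/2 = 0.20

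ANCOVA relative to change score: (1 − r²) / [2(1 − r)] = (1 + r)/2 = 0.65 / 0.75 / 0.85 / 0.95 at the four values of r. ANCOVA relative to follow-up only: 1 − r² = 0.91 / 0.75 / 0.51 / 0.19.

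**Identity of group-by-time and change score.** With two time points the rmANOVA group-by-time F equals the square of the change-score t. A numerical check on 20 simulated subjects gave F = t² = 0.6618.

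**Noncentrality.** For k = 1 it is 0.4 / (0.316 × √(2/10)) = 2.83. Each other test with the full effect divides this by √k. The group main effect starts from half, 1.41. ANCOVA also carries an approximate factor √(1 + 1/17) for estimating the slope and uses 17 rather than 18 error degrees of freedom. At r = 0.5, for example: change score 2.83/√1 = 2.83; ANCOVA 2.83/√(0.75 × 18/17) = 3.17; group main effect 1.41/√0.75 = 1.63.

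**Power at 10 per arm, σ = SD of one recording**

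| r | ANCOVA | Change score or group-by-time | Follow-up only | Group main effect |
|---|---|---|---|---|
| 0.3 | 0.78 | 0.62 | 0.76 | 0.38 |
| 0.5 | 0.85 | 0.76 | 0.76 | 0.34 |
| 0.7 | 0.95 | 0.93 | 0.76 | 0.31 |
| 0.9 | 1.00 | 1.00 | 0.76 | 0.28 |

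A simulation of 20,000 trials at each r agrees with the table to within about 0.01, and gives a mean group-main-effect estimate of 0.20.

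**Sensitivity: σ = SD of the change.** The SD of one recording is then 0.316/√(2(1 − r)). Change-score power is 0.76 at every r. ANCOVA gives 0.90 / 0.85 / 0.80 / 0.76 and the group main effect 0.50 / 0.34 / 0.20 / 0.09. The pattern for ANCOVA is the same: a gain of about 13 points at r = 0.3, falling to none at 0.9.

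**The case against.** The strongest reply is that baseline is already in the analysis. The endpoints and the analysis headings are all worded as changes, and item 5) Analysis crosses arm with before and after. The natural reading is therefore a t-test on changes in Study 1 and group-by-time in Study 2. Both subtract baseline, and under randomisation both are unbiased. This stands: a reader might infer that the protocol ignores baseline, and it does not.

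A reader might also infer that the trial will test the group main effect and so estimate half the treatment effect. The protocol never names that term as the treatment test, and it would not answer a question about change. The same holds for a t-test on follow-up values alone. Both are possible under the wording, but neither is stated, so their power figures show what the wording leaves open and not what is planned.

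It is also fair to say that the gain from ANCOVA depends on an r that the protocol does not give, and that it vanishes when r is high. Nor should it be said that change scores fail to deal with chance baseline imbalance. They remove the difference; what remains, given the imbalance actually seen, is regression to the mean, which shrinks as r rises.

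Finally, covariates and model terms are often left to a statistical analysis plan, and one may exist. This carries less weight here, because the protocol itself names the between-arm tests, so a plan specifying ANCOVA would depart from it. No defect in the protocol calls for a log transformation, and none is asked for.

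**Conclusion.** The point holds as one of efficiency and clarity, and not as an error that invalidates the comparison. The named between-arm tests omit baseline as a covariate although the recording is available for everyone.

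Against the change-score reading, the power gain from ANCOVA at the planning effect is about 16 points at r = 0.3, 9 at 0.5, 2 at 0.7 and none at 0.9. Against a follow-up-only t-test it would be about 2, 9, 19 and 24 points (ANCOVA power less 0.76). The group main effect would be far worse, at 0.28 to 0.38.

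These figures rest on the planning difference of 0.4, a common SD of 0.316 for one recording, and an assumed r. If 0.316 is instead the SD of the change, the gain over change scores is about 13, 9, 4 and 0 points.

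A reader might infer that 10 per group is therefore wrong. It is not: the stated figure is reproduced from its inputs, and this point leaves it unchanged.

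**What to change.** In item 11) Method of analysis, for both studies, make the between-arm test an ANCOVA of the follow-up value on treatment with the subject's own baseline as covariate. Report the adjusted difference and its 95% confidence interval.

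- **Study 1:** one model for the second EEG and one for the third, each with the first EEG as covariate.
- **Study 2:** the TMS value after 7 days, with the pre-dose value as covariate.
- **Where rmANOVA is kept** (for example across bands and locations): name group-by-time as the treatment term.

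The cost is a change of wording and one of 18 error degrees of freedom. At r near 0.9 that loss roughly cancels the gain over change scores (0.757 against 0.763 if 0.316 is the SD of the change). No extra subject, visit or recording is needed.

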**2) Hypothesis and objectives**

To evaluate the impact of celecoxib on cortical excitability and electrophysiological properties of the brain in healthy humans by electroencephalography (EEG) and transmagnetic stimulation (TMS), as ample evidence based on animal models of epilepsy has demonstrated that celecoxib has anticonvulsant effects.

◎ Primary object

- To evaluate the change of cortical excitability and electrophysiological properties in brain cortex to single oral dose of celecoxib (400mg once) in healthy volunteer

- To evaluate the change of cortical excitability and electrophysiological properties in brain cortex by long-term treatment of celecoxib (200mg twice-daily for 7 days) in healthy volunteer

◎ Secondary object

- To investigate the electroencephalographic changes by celecoxib in different locations and different frequency band.

1. **Study drug (generic name and brand name), dosing, dosage forms**

◎ Study drug

- Generic name: Celecoxib

- Brand name: Celebrex^®^

- Dosing and dosage forms: 200mg capsule

◎ Medical device

- EEG

Conventional EEG (10-20 system), (Grass-Telefactor, USA)

- Motor evoked potential (transcranial magnetic stimulation. TMS)

Magstim 200 devices (Magstim Co. Ltd., Dyfed, S. Wales, UK).

A figure-of-eight shaped magnetic stimulator (type 9925, maximal output 2.2 Tesla)

1. **Eligiblity criteria of subjects and sample size estimation**

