**4) Items of observation and methods**

**Study**

◎ Epidemiologic data

- Age, date of birth, age

- Medication history

- Medical history

- Physical examination

◎ Laboratory data

- Blood lab: AST/ALT, serum creatinine, potassium

- EKG

**-** EEG

- According to the international 10-20 system for 15 miniutes

- EEG (power spectra analysis)

The EEG data will be bandpass filtered (0.5-50 Hz) after re-referenced to the common average reference for analysis, and 10 epochs of 1.5 seconds in duration in the eyes-closed state without artefacts will be chosen. For power spectral analysis, the electrodes will grouped into frontal, central and parietal regions and analyzed by band width.

| Primary end point  - Change of power spectra by single high dose of celecoxib.  Secondary end point  - Change of power spectra by 7-day treatment.  - Change of electroencephalographic properties by celecoxib in specific locations or frequency band by single dose or 7-day treatment. |
| --- |

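### Study 2 tests five undifferentiated primary measures at an unadjusted 5% each, and Study 1 does not settle which time point or spectral variable is primary

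*Protocol*

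**What the plan says.** **Study 2.** The Study Summary (efficacy evaluation) and Section 11, 4) give the same single primary endpoint: "Change of resting motor potential, amplitude of MEP, cortical silent period, intracortical inhibition and intracortical facilitation by 7-day treatment of celecoxib". That is five measures. Neither place ranks them or says whether one or all must show an effect. MEP amplitude is recorded at "stimulus intensities of 120%, 140%, and 150% (if possible) of RMT". Section 11, 11), Study 2, plans paired tests within arm and rmANOVA between arms, and adds: "A two-sided 5% significance level will be used for all statistical differences". The Study 1 paragraph carries the same rule.

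**Study 1.** Both endpoint lists (Study Summary and Section 11, 4)) name as primary "Change of power spectra by single high dose of celecoxib" and as secondary "Change of power spectra by 7-day treatment". Also secondary is "Change of electroencephalographic properties by celecoxib in specific locations or frequency band by single dose or 7-day treatment". The objectives differ. In the Study Summary, the primary objectives for Study 1 include the single-dose effect and also the effect "by long-term treatment of celecoxib (200mg twice-daily for 7 days) in healthy volunteer". Section 8, 2) repeats both primary objectives without separating the two studies. In the Summary, the 7-day objective is also the only objective of Study 2.

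**Sample size.** Section 10, 3) uses a mean difference of 0.4, standard deviations of 0.4 and 0.2, a 5% level and power 0.8 to reach 10 per group, 40 in all.

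**The concern.** When five measures share the primary label, each is tested at 5% and no success rule is given, any one significant result can be reported as a positive primary outcome. The 5% then no longer describes the risk of a false primary claim for the study. The rmANOVA does not remove the problem: a threshold intensity, an amplitude and a duration are not on one scale, so each needs its own analysis.

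In Study 1 the objectives and endpoints disagree about the 7-day effect, so either time point could be presented as primary once the data are known. The primary endpoint refers to power spectra in general and gives no single variable to compare between arms. The protocol intends the results as a basis for later clinical work on celecoxib as an anticonvulsant, so what counts as a primary finding matters.

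**Working it through.** **Reproducing the plan's sample size.** Inputs from Section 10, 3): δ = 0.4, SDs 0.4 and 0.2, two-sided α = 0.05, power 0.8.

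n per group = (0.4² + 0.2²)(1.960 + 0.842)² / 0.4² = 0.20 × 7.849 / 0.16 = 9.81, rounded up to 10; 4 × 10 = 40.

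The stated figure is reproduced, and it is for one comparison at an undivided 5%. At 10 per group the power is 80.7% by the normal approximation and 76.3% by the t distribution.

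**Study 2, five measures at 5% each.** If independent, the chance of at least one false positive is 1 − 0.95⁵ = 22.6%.

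The protocol gives no correlations, so a range is assumed. Simulated two-sample t-tests with 10 per arm, equal pairwise correlation r and no true effect give:

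| r | At least one of five significant |
|---|---|
| 0 | about 22–23% |
| 0.3 | about 21% |
| 0.5 | about 18% |
| 0.7 | about 15% |
| 0.9 | about 10% |

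The within-arm paired tests, also at 5%, are not counted.

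**Study 1, two time points at 5% each.** If independent: 1 − 0.95² = 9.75%. The simulation gives about 9% at r = 0.5 and about 8% at r = 0.7.

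**Study 2 with control over the five measures.** Bonferroni, and the first step of Holm, use 0.05/5 = 1%. Family error under independence is 1 − 0.99⁵ = 4.9%. On the plan's inputs with 10 per group:

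- Power for one endpoint at 1% is 49.7% (t) or 60.0% (normal approximation).
- 80% power at 1% would need 17 per group (t) or 15 (normal approximation).
- If all five effects were real and each of the planned size, Holm's average power per endpoint is about 60%. The chance of at least one success is about 66 to 91% for r from 0.9 to 0.3.

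Section 10, 3) does not say which variable the 0.4 refers to, so applying it to every endpoint is an assumption.

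**The case against.** This is a phase 1 study of 40 healthy volunteers with no close precursor. It makes no explicit confirmatory claim, and multiplicity procedures are often left to the SAP, which is not at hand. A nominal 5% could in principle apply to adjusted p-values. The setting does limit how much rests on any one result. But the choice of primary endpoint belongs in the protocol, and a 5% level for every difference reads naturally as unadjusted. The point therefore rests on what the protocol states, not on something it leaves out.

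A reader might infer several stronger claims that the document does not support:

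- **That Study 1's primary error is 46% or 71%.** These are 1 − 0.95¹² and 1 − 0.95²⁴, for 4 bands × 3 regions at one or two time points. Band and location effects are declared secondary, and Section 11, 11) handles them by rmANOVA: "Analysis of EEG data will consider frequency bands (alpha, delta, theta and beta) and locations (frontal, central and parietal"). It does not prescribe 12 or 24 separate primary tests. The figures would apply only if those cells stood in for the unspecified primary variable.
- **That Study 2 has seven primaries and a 30% error** (1 − 0.95⁷ = 30.2%). MEP amplitude is one listed item, stimulus intensity can be a factor in the rmANOVA, and the highest intensity is conditional. This is a worst case.
- **That Study 1 has two primary endpoints.** Both endpoint lists agree that the single dose is primary. The mismatch lies in the objectives, and its cost is about twofold at most.
- **That the 7-day objective in Section 8, 2) should simply be demoted.** That section is not split by study, so this would also demote the only objective of Study 2.

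**Conclusion.** The point holds for Study 2 on the protocol's own wording. Five primary measures, no success rule and an unadjusted 5% give a false-primary chance of 22.6% under independence and about 15 to 21% at correlations of 0.7 to 0.3, roughly three to four and a half times nominal. At a correlation of 0.9 it is about 10%, twice nominal. The correlations are assumed.

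For Study 1 the finding is narrower. The Study Summary's primary objectives conflict with both endpoint lists over the 7-day effect, worth about 8 to 10% if both time points count. The primary endpoint also needs one named spectral variable. The document does not show a larger primary error than that. The sample size supports one comparison per study, not five.

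**What to change.** **Study 2.** Name one primary TMS variable and make the others secondary, or keep all five under Holm at a family 5%. If resting motor threshold is chosen, first reconcile the endpoint wording, which refers to a resting motor potential, with Section 11, 4), which defines a threshold.

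**Study 1.** Name one spectral summary as primary: second minus first EEG, celecoxib versus placebo. Move the 7-day objective to secondary in the Study 1 block of the Study Summary. Split Section 8, 2) by study so that the 7-day objective remains primary for Study 2.

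**Both.** In Section 11, 11), limit the unadjusted two-sided 5% to each study's primary test, and report band, region and other TMS results as exploratory.

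**Cost.** Fewer results can be called primary. With one primary per study, n = 10 per group still follows from the plan's own formula. Under Holm, power for a single real effect at the 1% first step is about 50% (t) on the plan's inputs, with higher average power if several effects are real. That favours a single primary variable.
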